### Data collection procedures and participant pathway

Data will be collected for all women who consent to participate using electronic case report forms (eCRFs) we developed for the study and programmed with Open Data Kit Collect (University of Washington, Department of Computer Science and Engineering, Seattle, WA, USA; https://opendatakit.org/) on Tecno PhonePad 7II tablets (TECNO Mobile, Hong Kong, China; www.tecno-mobile.com). A summary of the schedule of enrollment, interventions, and assessments is shown in Table 4. We trained study staff on data collection using the eCRFs prior to the start of recruitment. We will routinely assess the data throughout the study for inconsistencies and common errors as well as to identify missing values or missing records. We will resolve missing data to the greatest extent possible.

**Table 4 Tab4:** Schedule of enrollment, interventions, and assessments

	Study period					
	Enrollment	Allocation	Postallocation			
Time point^a^	Day 0	Day 0	Day 0	Day 3	Day 7	Day 42
Enrollment						
Eligibility screen	X					
Informed consent	X					
Allocation		X				
Interventions						
Procedure by CO			X			
Procedure by AMO			X			
Assessments						
Pregnancy test	X					
Directed physical examination	X			X	X	X
Adverse events			X	X	X	X
Interview					X	X

*AMO* Assistant medical officer, *CO* Clinical officer

^a^In most cases, screening, enrollment, allocation, and the tubal ligation by minilaparotomy procedure will all be done on the same day (designated as day 0)

After informed consent has been obtained by a research assistant, a study provider will evaluate each potential participant for clinical eligibility according to the study inclusion and exclusion criteria noted above. If eligible, a research assistant will randomize participants, and the minilaparotomy procedure will be done on the same visit in most cases (or, if not, within 7 days of screening). Providers will conduct tubal ligation procedures according to the GOT guidelines [21]. We have not placed any restrictions on clinical care that a provider deems necessary for the health and well-being of study participants, although we will collect data on all relevant concomitant care and interventions provided before or during the procedure, as well as during the follow-up period.

We will ask participants to return for three scheduled follow-up visits at 3, 7, and 42 days postsurgery. A research assistant will call or text participants the day before each scheduled visit to remind them to come for follow-up. If a participant misses a visit, a research assistant will attempt to contact the participant three times to encourage him/her to come for the visit. We will give participants 5000 Tanzanian shillings (approximately $2.25) to cover time and transport cost to/from the study site for each of the three scheduled follow-up visits. A provider may schedule additional visits if clinically necessary, and we will inform participants that they should return to the site at any time if they have problems or concerns related to the procedure.

We will collect data at three time points:Prior to the minilaparotomy procedure, we will record detailed information on sociodemographic characteristics, obstetric and family planning use history, and physical examination findings.At the time of surgery, we will gather details of the anesthesia and procedure, including problems encountered, assistance needed, and occurrence of AEs.We will record information on physical examination findings, AEs, and participants’ experience and satisfaction postsurgery; during recovery; and at 3, 7, and 42 days after surgery, as well as during any unscheduled follow-up visits.At the end of the study, we will collect information from the COs and AMOs on self-efficacy, including measures of general self-efficacy, and confidence and comfort conduting minilaparotomy.

Once an individual eCRF is completed, a research assistant will encrypt the data on the tablets and upload it through a secure connection to the database located on a server in EngenderHealth’s office in Dar es Salaam, Tanzania. Detailed procedures for the collection, management, and use of the data are outlined in a study data management plan.

Providers will assess participants for the presence of AEs during the minilaparotomy procedure and postoperative period, as well as at all scheduled and unscheduled follow-up visits, and provide treatment/referral and follow-up as clinically indicated. We will collect detailed data on AEs in the eCRFs, including type, severity, relatedness to the minilaparotomy procedure, treatment, and outcome. We will report serious AEs resulting in death to the institutional review boards (IRBs) within 24 h of when the principal investigator (PI) is notified and those resulting in hospitalization within 10 days of notification of the PI.

We will also monitor for social harm events (SHEs) such as loss of privacy, stigmatization, relationship difficulties, physical or verbal abuse, and interference with gainful employment. We will help participants address any reported SHEs or refer them to available support services appropriate for the SHE. We will report SHEs potentially related to study participation to the IRBs within 10 days of when the PI is notified. During the study, an independent clinical trial monitor will conduct periodic on-site monitoring visits as needed to ensure that the study is being conducted and informed consent is being obtained according to the approved protocol, good clinical practice standards, and applicable regulatory guidelines, as well as to monitor recruitment and data quality.

### Statistical methods

We will develop a detailed analysis plan that covers both the final analysis and the planned interim analysis prior to initiation of the analysis. The primary outcome of the trial is major AEs within 42 days of the tubal ligation by minilaparotomy (i.e., the proportion of participants experiencing a major AE by day 42 postsurgery) in an intention-to-treat (ITT) analysis. We will conduct the primary analysis for the ITT population. The ITT population would include participants for whom the protocol is violated (i.e., participants who are randomized to have their procedure done by a CO but in fact have the procedure done by an AMO, or participants who are randomized to have their procedure done by an AMO but in fact have the procedure done by a CO) and withdrawals/discontinuations. We will also conduct a per-protocol analysis for the primary outcome if we have participants who do not receive the treatment to which they were randomly allocated.

Unlike a superiority trial, where the treatment effect is the primary parameter of interest, the interpretation of a noninferiority trial’s results depends on the location of the CI for the effect of the experimental treatment relative to the margin of noninferiority and a null effect [22]. The primary analysis will be interpreted as follows. If the whole 95% CI lies above the noninferiority margin of 2%, the experimental intervention will be declared “inferior.” If the whole 95% CI lies below the noninferiority margin, the intervention will be considered to be “noninferior” to the standard treatment. If the 95% CI includes the noninferiority margin, study results will be deemed inconclusive. Finally, if the entire 95% CI lies completely below zero, the new treatment may be considered superior to the standard treatment.

We will conduct other analyses on primary and secondary outcomes related to tubal ligation by minilaparotomy, including AE rates (overall and per time point), measures of performance (e.g., procedure times, difficulties performing the procedure, inability to complete the procedure), and participant satisfaction. We will analyze data on key demographic and reproductive variables (e.g., age, education level, marital status, occupation, ethnicity, parity) to generate a profile of study participants undergoing tubal ligation by minilaparotomy at study sites. We will analyze data on key provider-level variables to generate a profile of providers, disaggregated by provider type (CO and AMO). Methods of analysis for each secondary outcome are shown in Table 1 above.

We will include data in the analyses for all outcomes for participants who withdraw or are discontinued in the study through the time their study participation ends. We will not consider observations with missing data in the analyses and will not impute any missing data.

We have recruited a three-member data and safety monitoring board (DSMB) with no direct involvement in the study, including a surgeon experienced with tubal ligation by minilaparotomy, an epidemiologist, and a statistician. The role of the DSMB will be to deal with any ethical and safety issues that may arise during the trial and to review an interim analysis. We will conduct the interim analysis after approximately one-third of the sample has had the minilaparotomy procedure and completed the 7-day follow-up visit. At the time of the interim analyses, we will provide the DSMB with safety and study quality data (e.g., recruitment and follow-up rates, protocol violations), unmasked by treatment group.

We will ask the DSMB to give advice regarding stopping the trial if they have proof beyond doubt of an important advantage or disadvantage for one of the treatment groups and if they consider that the results are likely to affect clinical practice. For the primary outcome (i.e., major AEs), the following stopping guidelines have been proposed for the DSMB:At the time of the interim analysis, the DSMB may recommend stopping the study or temporarily halting recruitment if there are significantly more major AEs in one randomization group than in the other; a difference between the two treatment arms will be considered significant if the *p* value is < 0.001 [23].In the event that the interim analysis shows notably higher rates of major AEs in the study participants overall (i.e., both study arms) relative to the generally accepted AE rates following tubal ligation by minilaparotomy (e.g., a > 5% rate, which is the upper limit of the 95% CI in previously published studies), the DSMB may recommend stopping the study or temporarily halting recruitment.The DSMB may also recommend stopping the study, temporarily halting recruitment, or adjusting study sites if it seems that recruitment is not proceeding at rates that will allow the study to reach its target sample size within a reasonable time frame.

If the study is stopped temporarily or permanently for any reason, we will continue to follow participants already enrolled for the planned follow-up period (and longer, if necessary, based on clinical indications). We will continue to provide enrolled participants with clinical care as necessary. According to the charter agreed to by the DSMB members before the start of the trial, their role will be as advisors to the investigators; the latter will be responsible for making decisions regarding temporarily or permanently stopping recruitment.

The PI will have responsibility for informing relevant parties (e.g., other investigators, study site personnel, IRBs, trial participants, trial registries), or ensuring they are informed, of any important protocol modifications or other information pertinent to conduct of the trial via email or phone or in person in a timely fashion, depending on the nature and urgency of the information.

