## Methods/design

This study is a noninferiority randomized controlled trial (RCT) comparing the safety of tubal ligation by minilaparotomy conducted by trained COs and by trained AMOs in Tanzania. We will randomize a total of 1970 women 18 years of age and older presenting at 7 sites for tubal ligation in a 1:1 ratio to have the procedure done by a CO or an AMO. In addition to the screening and enrollment/tubal ligation visit, there will be three scheduled follow-up visits at 3, 7, and 42 days postsurgery. Figure 1 depicts the flow of study participants. We have included a Standard Protocol Items: Recommendations for Interventional Trials (SPIRIT) checklist in Additional file 1.

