### Outcome measures

The primary objective is to establish whether the safety of tubal ligation by minilaparotomy as provided by COs is noninferior to the safety of tubal ligation by minilaparotomy as provided by AMOs. The primary study outcome is safety, defined by the overall rate of major AEs observed during the procedure and through 42 days of follow-up. We will compare the rate of major AEs observed following procedures conducted by COs with that of procedures performed by AMOs. Major AEs include the following:Injuries to abdominal viscera, pelvic abscess, or severe peritonitis leading to unintended major surgerySevere intra- or immediate postoperative hemorrhage requiring blood transfusionFebrile morbidity (oral temperature > 38 °C on at least 2 postoperative days, excluding the first 24 h after surgery)Life-threatening event (including cardiopulmonary crisis or anaphylaxis)Readmission to the hospital any time after discharge after the procedure through the end of follow-up, owing to a complication related to the minilaparotomy procedureDeath or complication resulting in death occurring within 42 days of the surgery related to the minilaparotomy procedure

Secondary objectives and their outcomes include comparison of the following:The safety of tubal ligation by minilaparotomy provided by COs versus AMOs as measured by AE rates (major and minor) at different points in time (intraoperatively, immediately postoperatively, and at each follow-up visit)The performance (e.g., procedure times, difficulties performing the procedure, inability to complete the procedure, need for assistance to complete the procedure, and maximum reported pain experienced by the participant during the procedure) of COs versus AMOs for conducting tubal ligation by minilaparotomyParticipant satisfaction with the tubal ligation conducted by COs versus AMOsThe self-efficacy of COs versus AMOs in performing tubal ligation by minilaparotomy, defined by provider confidence, comfort, and perception of their ability to perform the procedure

Detailed definitions of the primary and secondary outcomes, including the domain (name of the outcome), specific measurement, metric, method of aggregation, and time point for measurement can be found in Table 1.

**Table 1 Tab1:** Definitions and statistical methods for analyzing primary and secondary outcomes

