### Generation of allocation sequence and random allocation

We used permuted blocks within the site for the randomization to ensure similarity of groups with regard to potential confounding factors. A researcher unaffiliated with the study generated by computer the random allocation sequence centrally at EngenderHealth headquarters in New York City. Randomization is in a 1:1 ratio (minilaparotomy conducted by a CO or minilaparotomy conducted by an AMO), stratified by study site, and restricted with randomly varying block sizes of four to eight within the strata. We will recruit participants at all study sites until the total sample size has been reached. A research assistant at each site will randomize participants after screening has been conducted, a woman’s eligibility for study participation has been confirmed, and just prior to start of the minilaparotomy procedure. We will achieve random allocation concealment by using a text message service (Sealed Envelope Ltd. [www.sealedenvelope.com], London, UK). Because of the nature of the services and low availability of clinical staff at study sites, it is not possible to mask participants, coinvestigators, those assessing outcomes, or other study staff to treatment allocation.

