Assuming a 3% major AE rate in the control group (AMOs), we will demonstrate noninferiority within the margin of 2% at a one-sided significance level of α = 0.05 and a power of 80% (calculated when AE rates in both arms are the same) with a sample size of 895 per arm (1790 women in total). Adjusting by 10% for loss to follow-up, protocol violations, and withdrawals, this would result in a total sample size of 1969 women, rounded to 1970.

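### Noninferiority is decided on the ITT analysis alone, which keeps women operated on by the other cadre, and a disagreeing per-protocol result could not change the conclusion

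*Protocol article*

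**What the plan says.** Methods/design sets the frame: "This study is a noninferiority randomized controlled trial (RCT) comparing the safety of tubal ligation by minilaparotomy".

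The Statistical methods section of the protocol article then fixes four things:

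- **Primary set.** "We will conduct the primary analysis for the ITT population".
- **Its content.** ITT keeps women whose procedure was done by the cadre they were not assigned to, in either direction, together with withdrawals and discontinuations.
- **Per-protocol.** "We will also conduct a per-protocol analysis for the primary outcome if we have participants who do not receive the treatment" to which they were allocated. It is therefore conditional on at least one such woman.
- **Decision rule.** The inferior, noninferior, inconclusive and superior readings are attached to the primary analysis, which is ITT. Noninferiority requires the whole 95% CI for CO minus AMO to lie below 2%.

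No sentence requires the per-protocol result to agree, and none says how a disagreement would be read. Among the secondary performance outcomes, Outcome measures lists "need for assistance to complete the procedure" and inability to complete it.

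**The concern.** In a superiority trial, ITT is the cautious choice because crossover pulls the difference toward zero. In a noninferiority trial the same pull works toward the claim. The article notes that a noninferiority result is interpreted differently from a superiority result, yet it carries over the superiority habit of letting ITT decide alone.

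If COs have a higher rate of major adverse events, each woman assigned to a CO but operated on by an AMO lowers the CO-arm rate, and each woman switched the other way raises the AMO-arm rate. Both narrow the gap. Under the rule as written, a per-protocol interval reaching past 2% would leave a noninferior verdict standing. The Discussion expects the result to bear on government regulation of who may operate, so that verdict matters.

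**Working it through.** **Inputs.** From the article: margin 2 percentage points; AMO rate 3%; 1:1 allocation; 1970 women, so 985 per arm; two-sided 95% CI rule. Assumed: a true CO rate of 5%, which puts the difference exactly at the margin, and a crossover share c, which the article does not give. Women who cross over are taken to have the average rate of the cadre that operates on them.

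**The plan's own figure first.** Power is "calculated when AE rates in both arms are the same", one-sided alpha 0.05, power 80%:

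n = (1.645 + 0.842)² × 2 × 0.03 × 0.97 / 0.02² ≈ 900 per arm

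The article states 895, which gives 79.8% power on this formula, so it is reproduced within rounding and choice of formula. 1790 × 1.10 = 1969, rounded to 1970.

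**Effect of crossover.** With a share c switching in each direction:

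- CO arm: pC = 0.05(1 − c) + 0.03c
- AMO arm: pA = 0.03(1 − c) + 0.05c (pA stays at 0.03 if only CO-to-AMO switching occurs)
- D = pC − pA
- SE = √[pC(1 − pC)/985 + pA(1 − pA)/985]
- Probability of declaring noninferiority = Φ((0.02 − D)/SE − 1.96)

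Worked case, c = 5% each way: pC = 0.0475 + 0.0015 = 0.0490; pA = 0.0285 + 0.0025 = 0.0310; D = 0.0180; SE = 0.00882; (0.0200 − 0.0180)/0.00882 = 0.227; Φ(0.227 − 1.96) = 4.2%.

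| c | D, two-way (points) | False noninferiority, two-way | D, CO-to-AMO only (points) | False noninferiority, CO-to-AMO only |
|---|---|---|---|---|
| 0% | 2.00 | 2.5% | 2.00 | 2.5% |
| 2% | 1.92 | 3.1% | 1.96 | 2.8% |
| 5% | 1.80 | 4.2% | 1.90 | 3.3% |
| 10% | 1.60 | 6.6% | 1.80 | 4.2% |
| 20% | 1.20 | 14.6% | 1.60 | 6.7% |

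The shift always favors noninferiority.

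**How the per-protocol set is built matters.** Suppose (assumed figures) the CO arm runs at 5% overall against 3% for AMOs, and 5% of CO procedures are finished by someone else, with a 20% event rate among them. Excluding those cases leaves a CO rate of (0.05 − 0.05 × 0.20)/0.95 = 4.2% and a difference of 1.2 points. With 985 AMO and about 936 CO women, SE = 0.0085, and per-protocol alone would declare noninferiority about 15% of the time. With a 10% event rate among the excluded cases it would be about 4.8%. ITT, which keeps them, stays at 2.5%. Excluding taken-over cases therefore weakens the per-protocol check exactly where it is meant to help.

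**Power cost.** If the per-protocol set lost the whole 10% allowance, 985 × 0.9 ≈ 886 per arm would remain. Power at equal 3% rates under the 95% CI rule is then about 69%, against about 74% at 985. Requiring both sets to pass gives slightly less than the lower figure. (That both fall below 80% comes from sizing at one-sided 0.05 while deciding on a two-sided 95% CI, which is a separate matter.)

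**The case against.** The best case for the plan is that ITT as primary with per-protocol in support is a legitimate choice, that a detailed analysis plan is promised, and that silence on discordance does not mean a discordant result would be ignored. The definition of the per-protocol set can indeed be left to that plan. The decision rule was not left to it: the article states the rule in full and ties it to one population. Requiring both sets would change that rule.

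Other objections stand and limit the point:

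- **The conditional trigger is not a defect against crossover.** One crossover triggers the per-protocol analysis. With none, a set defined by treatment received equals ITT.
- **Crossover is provided for, not forecast.** The wording is contingent and no rate is given. Randomization takes place just before the procedure, which leaves little time to switch.
- **Takeover by AMOs is not documented.** A reader might infer from the assistance and non-completion outcomes that AMOs will finish difficult CO cases. The article does not say who assists or completes. Under Study sites it says that physicians outside the study normally provide the procedure at these facilities. It also does not say that the finishing cadre is recorded.
- **The arithmetic models average switching, not selective takeover.** In ITT, a hard case handed over stays charged to the CO arm, including any injury before handover.
- **Per-protocol has its own selection bias**, as the takeover illustration shows. It can supplement ITT but should not replace it.

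**Conclusion.** The point holds as a weakness in a decision rule that the article itself fixes: ITT alone decides, crossovers stay in it, and per-protocol has no stated bearing on the conclusion. The direction is certain if COs are truly worse and women who switch take on the operating cadre's rate. The size is not certain. False noninferiority stays at or below 3.1% for crossover up to 2%. It reaches 4.2% at 5% two-way or 10% CO-to-AMO crossover, and 6.6% at 10% two-way, all against a nominal 2.5% and all on assumed crossover rates.

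A reader might go further and conclude that the trial's error rate is in fact inflated, or that a noninferior result would rest on AMO work. The article supports neither, because it gives no crossover rate and describes no takeover by the other cadre. The change is worth making because it is cheap and can only tighten the claim. If crossover is rare, little would have been lost without it.

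**What to change.** In the decision rule, state that noninferiority is claimed only if the upper limit of the two-sided 95% CI for CO minus AMO is below 2% in both the ITT and the per-protocol analyses, and that discordant results are reported as inconclusive. The analysis plan, which the article says will be written before analysis begins, can carry this.

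In the per-protocol definition, keep a procedure started by the assigned cadre and finished by another in the starting operator's arm, and add a sensitivity analysis that excludes such procedures. This needs the starting and finishing operator for each procedure. The article says assistance needed is recorded at surgery, so check whether the cadre is recorded too.

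The existing trigger for the per-protocol analysis need not change for crossover.

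The cost is a few sentences and no new sample size input, since the 10% allowance already names protocol violations. Power falls slightly if crossovers are common (roughly 74% to 69% if the whole allowance were used up) and hardly at all if they are rare, because the two sets then nearly coincide.
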